### Data collection

For all patients background information is collected from the EHRs at T0. This includes age at inclusion, histological type and grading of ovarian cancer, FIGO stage, type of treatment, end date of treatment, smoking status and body mass index.

To evaluate the intervention, data will be collected to (1) analyse patient and HCP experiences with CopA, (2) investigate implementation barriers and facilitators using qualitative methods and (3) process evaluation of the intervention, assessing components such as reach, fidelity and compliance, time to response and number of (tele)consultations during the study period. The study coordinator will keep a logbook of all small adjustments that will be made during the implementation.

#### Patients and HCPs’ experiences with CopA

The experience of HCPs working with remote ambulatory monitoring of ovarian carcinoma, that is, oncological nurses, oncologists and gynaecologists, will be assessed using the Measurement Instrument for Determinants of Innovations (MIDI) questionnaire. This questionnaire is designed to evaluate the implementation of an innovation such as guidelines, protocols and digital technology.^25^ An adapted version of the MIDI will be distributed after the first moment of implementation (T0) to investigate HCPs’ *expectations* about working with remote monitoring and the possible barriers they think they might encounter.^24^ This adapted version includes only the relevant questions that HCPs are able to answer at the start of the project (expectations). After 6 (T1) and 12 (T2) months, the questionnaire will be sent again to assess actual experience. The MIDI questionnaire at T0, T1 and T2 will be used to determine if implementation barriers and facilitators change over time. The MIDI questionnaire covers four different domains, that is, the innovation itself (CopA), the user (HCP and patient), the organisation (the hospital) and the context (society).

Patients will receive the Experienced Usability and Satisfaction with self-monitoring in the home Setting (GEMS) questionnaire at T1 (6 months) and T2 (12 months). This validated questionnaire is designed to measure experienced usability and satisfaction of patients with self-management tools.^26^ The GEMS comprises four subscales: Convenience of use, Perceived value, Efficiency of use and Satisfaction. Each subscale consists of two items with a Likert scale from 1 to 5 (completely disagree to completely agree), except for the Satisfaction subscale, which consists of three items. Two of the items on the Satisfaction subscale have a Likert scale from 1 to 10.

Text box 1 provides a short overview of measurement instruments. In the online supplemental file II, we outlined the measurement instruments MIDI and GEMS in more detail, including response categories.

Box 1Short overview of questionnaires distributed at various moments in time to patients and HCPs who are involved in remote FU care for ovarian cancer
*For healthcare professionals*
T-0hcpBaseline demographics: Age, gender, specialism in medicine, number of years working in the field.Adapted version of the MIDI questionnaire (*expectations*), including only relevant barriers/facilitator questions related to expectations of working with the technology.Thcp-1 (after 6 months)Full MIDI questionnaire to identify barriers/facilitators based on experience with remote ambulatory monitoring.Short interviews with participating HCPs to clarify the identified barriers/facilitators including any problems they encounter when using remote monitoring, and to collect suggestions for improvement of ovarian cancer monitoring via the EHR/patient portal.Thcp-2 (after 1 year)Full MIDI questionnaire to identify barriers/facilitators based on experience with the technology and to compare changes over time.
*For patients*
T-0pBaseline demographics: Age, gender, education level*, digital literacy**, health literacy**.QoL data from the EORTC QLQ C30 and OV-28.Tp-1 (6 months after start of follow-up care)GEMS questionnaire: experienced usability and satisfaction after working with self-management via patient portal.Focus groups will be held with patients to clarify the results including any problems they have when using the system, and to collect suggestions for improvement of ovarian cancer monitoring via the EHR/patient portal.QoL data from the EORTC QLQ C30 and OV-28.Tp-2 (1 year after follow-up care)GEMS questionnaire.QoL data from the EORTC QLQ C30 and OV-28.EORTC Core Quality of Life Questionnaire (EORTC QL), HCP: Healthcare professional, Thcp:, MIDI: Measurement Instrument for Determinants of Innovations, OV-28: Ovary - 28, QoL: Quality of Life; GEMS: Experienced Usability and Satisfaction with self-monitoring in the home Setting.*Educational level is assessed according to the Dutch system, including categories no formal education; less than high school; high school diploma, some college, bachelor’s degree and graduate degree.**Digital literacy is assessed using one question as part of the validated GEMS questionnaire; health literacy is assessed as self-reported health literacy using the three validated questions by Chew et al. (2008).

Data collection of questionnaires will be done electronically by e-mail using Castor EDC. This is an electronic data capture platform designed to streamline the process of collecting, managing and analysing research data.

#### Identification of barriers and facilitators to implementation

Based on the results of the GEMS questionnaires and the MIDI questionnaires (see 1), in-depth interviews with HCPs and focus groups with patients will be performed to gain more insight into experiences, but also barriers and facilitators of the use and implementation of CopA in clinical practice. At the time of inclusion, patients are able to provide consent to be approached for additional focus groups. All patients who participate in CopA for at least 6 months and provide consent will be invited to a focus group (4–8 participants). For patients who relapsed, we will ask the treating physician if it is appropriate to approach the patient. We aim at organising two focus groups. All participating HCPs will be invited for a semi-structured interview after filling out the MIDI questionnaire at T1 (6 months). Both the focus groups and interviews will be conducted by researchers who are not involved in patient care and have experience in performing semi-structured interviews and leading focus groups. Both interviews and focus groups are audio-recorded and transcribed literally.

#### Process evaluation of CopA

For the process evaluation, we follow the model of Linnan and Steckler.^27^ This is a commonly used tool to evaluate the process of the implementation of eHealth interventions systematically because it describes the adherence to the intervention in five terms: (1) the proportion of intended target audience that participated in the study—reach, (2) the number of intended units of each component that was delivered—dose delivered, (3) the number of participants that actively engaged the delivered components of the intervention—dose received, (4) the extent of the intervention that was delivered as planned—fidelity and (5) participants’ satisfaction and usage barriers of the intervention—participants’ attitudes. Data for this process evaluation were collected from the patients using online questionnaires at T0, T1 and T2 and using qualitative methods as described above. In addition, data were also obtained from patients records and by means of an automatically generated weblog of the EHRs. Table 3 gives an overview of these process measures.

**Table 3 T3:** Process measures, definitions and data collection methods

Process measure	
*Reach* Proportion of the target population that received the intervention	*Definition* Proportion of recruited potential participants that met all inclusion criteria and decided to engage in the study
	*Data collection method* Study database Weblog
*Dose delivered* Proportion of intended intervention that was actually delivered to target population	*Definition* Proportion of study population that received an account for the patient portal and first invitation to fill out PROMs
	*Data collection method* Weblog
*Dose received* Extent to which the participants used the intervention as recommended	*Definition* Proportion of patients with an account that used the patient portal to fill out PROMs and/or home measurements at least once
	*Data collection method* Weblog
*Fidelity* Extent to which the intervention was delivered as planned	*Definition* Proportion of patients who participated in the study for at least a year and received their 6 month appointment Time to response of the nurse to the measurements Number of (telephone) consultations during the study period
	*Data collection method* Weblog Patient records
*Participants’ attitudes* Satisfaction Perceived effectiveness Usage barriers Suggestions for improvement	*Target* Patients Gynaecologists and nurses
	*Data collection method* Interviews and focus groups MIDI questionnaire HCPs GEMS questionnaire patients

GEMS, the Experienced Usability and Satisfaction with self-monitoring in the home Setting questionnaire; HCP, healthcare professional; MIDI, Measurement Instrument for Determinants of Innovations; PROMs, patient-reported outcome measures; Weblog, data extracted from the EHR.

##### Reach

Reach concerns the degree to which an intended audience participated in the intervention. The research team identifies from the EHRs which patients finish treatment for ovarian cancer and enter follow-up. We register what proportion of these patients decides to participate in the study and who declines. Reasons for exclusion will be registered, as well as the number and reasons for drop-out during the study.

##### Dose delivered

Dose delivered refers to the proportion of the intended intervention that is actually delivered to the participants. The number of patients that received the online invitation after 3 months to fill out PROMs divided by the total number of participating/included patients was defined as dose delivered.

##### Dose received

Dose received is a measure of the extent to which participants actively engage with the intervention. Dose received was defined as the proportion of patients that used the intervention as recommended, that is, they filled out the PROMs and home measurements at least once. In addition, we monitor if patients had contact with the nurse practitioner either through an e-consult or telephone consultation.

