##### Procedures and work flow

CopA is initiated with a designated hospital visit at the end of treatment. During this visit, explanation and information are provided about CopA. An instruction video is available on how to perform the home measurements.Three-monthly, patients receive an automatic invitation to complete the PROMs in the patient portal (MyChart) of the EHR (table 1) and to measure and provide their weight and abdominal circumference. The invitation for completion is sent 14 days before the deadline, giving patients the freedom to complete the survey in their own time. Completion is encouraged through reminders sent through email/online application 1 week before the deadline. Patients will answer the questionnaire based on their perception of their current well-being. Patients can access the patient portal and home monitoring system at any time.On the hospital side, a daily report is created of the patients that have completed a new series of PROMs. It allows the oncological nurse to evaluate the responses to the PROMs and take appropriate actions if indicated. Table 2 shows the type of action required for the different types of alerts. An alert is generated in the EHR, visible to the oncological nurse when the predefined thresholds are exceeded, indicating a need for intervention. An active approach is used wherein the HCP is instructed to contact the patient within 48 hours. The nurse specialist will contact the patient to together decide on the best course of action (ie, visit to the hospital, referral to other HCPs or watchful waiting). The patient also has the option—at the end of the questionnaire—to state that contact from the hospital is not needed or preferred. Patient representatives requested this option, which is in line with patient preferences in another comparable study among lung cancer patients that strongly preferred this option to be added.^10^

**Table 2 T2:** Possible actions based on home measurement outcomes

No threshold(s) exceeded and no specific wish for contact*	The nurse sends a message to the patient that no further action is needed and that values and answers to PROMs look good.
No threshold(s) exceeded, but explicit wish for contact	(Nurse will discuss with the gynaecologist or oncologist.) The nurse sends a message to the patient that the values and answers look good, but that the patient will be contacted for an appointment/ patient can make an appointment.

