Threshold(s) exceeded, but wish for no contact	(Nurse will discuss with the gynaecologist or oncologist.) The nurse sends a message to the patient that some of the values or answers exceed the threshold, and that this might be a reason for contact with the nurse or doctor. However, as the patient indicates no need for contact, an appointment will not be made. The patient will be informed that they can always seek contact if they change their mind based on this information.
Threshold(s) exceeded and open for contact	(Nurse will discuss with the gynaecologist or oncologist.) = Thresholds exceeded⇒patient is contacted by nurse by telephone for further action.
Patient failed to complete PROMs	An alert will be sent to the oncological nurse. The patient receives another online reminder. When there is no response, the nurse will call the patient after 1 week at the latest.

* Patients will have the option to click ‘no contact wanted’ which may be used when the patient prefers self-management or if symptoms reflected in the PROMs may have an external cause; eg, mood.

PROM, patient-reported outcome measure.

Based on the outcomes of filled out PROMs and/or contact with the nurse, patients might need support from a HCP outside of the hospital, that is, physical therapist or dietician. In the patient portal, a link to a website with a comprehensive list of information is made available for patients helping them to find the appropriate HCP nearby their home. They can consult this list at any time in their portal facilitating self-management when patients notice a problem based on the PROMs they fill out, regardless of exceeding a threshold.Patients always have the option to call the hospital when experiencing problems.Patients will have one hospital visit after 6 months.

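### Dose received is defined differently in the text and in Table 3, and both definitions count a single completion as use as recommended under a 3-monthly schedule

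*Protocol article*

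**What the plan says.** Protocol article, Dose received: the measure is the proportion of patients who "used the intervention as recommended, that is, they filled out the PROMs and home measurements at least once". Both components are required, and no account restriction is stated.

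Protocol article, Process evaluation of CopA, Table 3: the same measure is labelled "Extent to which the participants used the intervention as recommended" and defined as "Proportion of patients with an account that used the patient portal to fill out PROMs and/or home measurements at least once". Either component is enough, and the denominator is limited to account holders.

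Protocol article, Procedures and work flow: "Three-monthly, patients receive an automatic invitation to complete the PROMs in the patient portal (MyChart) of the EHR". The same invitation asks for weight and abdominal circumference. Reminders follow, and for non-completers Table 2 adds: "When there is no response, the nurse will call the patient after 1 week at the latest".

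Protocol article, Fidelity: the text counts patients who completed PROMs at each 3-monthly point for a year or more and had the 6-month appointment. Table 3's fidelity row asks only for a year's participation and that appointment, plus nurse response time and consultation counts.

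**The concern.** Two problems sit in one measure.

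- **Label.** What CopA recommends is a repeated task. A patient who completes the first round and then stops counts the same as one who completes every round, and both are reported as having used the intervention as recommended.
- **Rule.** Text and table differ on the conjunction and on the denominator, so the same data can give different percentages depending on which is followed.

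CopA is meant to stand in for 3-monthly visits, so whether patients keep completing rounds bears directly on feasibility. Someone who reads the dose-received percentage under its present label would take it as evidence of continued use, which it cannot provide.

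**Working it through.** The protocol states no expected value, target or completion rate for dose received, so there is no figure to reproduce. The check asks how far an at-least-once measure can depart from the share of rounds completed.

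**Inputs**
- Rounds per year: 12 months / 3 months = 4 (Procedures and work flow).
- Planned patients: 50 (Sample size).
- Completion probability per round, p: not in the documents; assumed, 0.1 to 0.8.
- Within-patient correlation, ICC: not in the documents; assumed, 0, 0.3 and 0.5.

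**Formulas**
- Independent rounds: P(at least one of 4) = 1 − (1 − p)^4; P(all 4) = p^4.
- Correlated rounds: beta-binomial with a = p(1 − ICC)/ICC and b = (1 − p)(1 − ICC)/ICC. P(none of 4) is the product of (b + i)/(a + b + i) for i = 0 to 3.

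**Worked case, p = 0.5**
- Independent: 1 − 0.5^4 = 93.8% at least once; 0.5^4 = 6.3% all four.
- ICC 0.3: a = b = 1.167. P(none) = 0.5 × 0.65 × 0.731 × 0.781 = 0.186, so 81.4% at least once. By symmetry, 18.6% complete all four.
- Share of rounds completed: 50% in both cases.

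**At least one of 4 rounds, over the assumed range**

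| p (share of rounds completed) | Independent | ICC 0.3 | ICC 0.5 |
|---|---|---|---|
| 0.1 | 34.4% | 24.3% | 19.4% |
| 0.2 | 59.0% | 44.0% | 36.2% |
| 0.3 | 76.0% | 59.7% | 50.5% |
| 0.5 | 93.8% | 81.4% | 72.7% |
| 0.7 | 99.2% | 93.4% | 87.7% |
| 0.8 | 99.8% | 96.7% | 93.0% |

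If the same patients always or never respond, the measure equals p.

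**Limiting case.** If 50 patients each complete exactly one of four rounds, dose received is 50/50 = 100%, while rounds completed are 50/200 = 25%.

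**Conjunction.** Assume per-round completion of 0.6 for PROMs and 0.4 for home measurements, independent, over 4 rounds.
- PROMs at least once: 1 − 0.4^4 = 97.4%. Home measurements at least once: 1 − 0.6^4 = 87.0%.
- Table 3 rule (either): 1 − 0.4^4 × 0.6^4 = 99.7%.
- Text rule, both at some time: 0.9744 × 0.8704 = 84.8%.
- Text rule, both in the same round: 1 − (1 − 0.24)^4 = 66.6%.

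With 0.8 and 0.5 instead, the three figures are 100.0%, 93.6% and 87.0%.

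**The case against.** The strongest defence is that the framework, as the protocol describes it, treats dose received as the number of participants who actively engaged, and places delivery as planned under fidelity. Counting ever-users in one measure and sustained completers in the other is a reasonable split. The Fidelity text does count PROMs at each 3-monthly point for a year. In the worked case with p = 0.5 and independence, it could not exceed 6.3%, so falling engagement would show. Drop-outs and their reasons are also recorded (Reach). Dose received is one of five descriptive measures and has no target or decision rule attached.

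Much of this stands. A reader might infer that dose received will be near 100% whatever the real use, that dose delivered is too, and that the process evaluation as a whole would report success for a programme most patients abandon. The documents support none of these:
- The table above shows 34% to 76% at 10% to 30% per round under independence, and less when non-use clusters in the same patients. Patients who never start count as failures.
- Dose delivered counts patients who "received the online invitation after 3 months to fill out PROMs" over all included patients. Reminders and nurse calls come after the invitation and cannot raise it, and recurrence or return to standard care before 3 months can lower it.
- The Fidelity text would show poor sustained PROM completion if it is the definition used.

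The defence does not cover three things. The as-recommended label is still attached to a single completion. Table 3's fidelity row drops the 3-monthly PROM criterion, so if the table governs, no listed measure captures sustained completion. And neither fidelity version counts repeated weight or circumference measurements, which are part of every round.

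**Conclusion.** The point holds in limited form. Dose received measures first use, is labelled as recommended use, and has two conflicting definitions. The contradiction in conjunction and denominator, and the mismatch between label and schedule, can be read directly from the protocol and need no assumption.

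The size is conditional. With 50% of rounds completed over a year, the measure would read about 94% under independence, 81% at ICC 0.3 and 73% at ICC 0.5. It therefore has a ceiling when completion is moderate or high, and none to speak of when uptake is low or concentrated in the same patients. The choice of conjunction alone could move the figure from 99.7% to between 66.6% and 84.8% under the assumed component rates. The reminders and nurse calls make a high value plausible but do not guarantee it.

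For engagement over time, the pilot can conclude something about PROMs only if the Fidelity text is followed rather than Table 3, and nothing about repeated home measurements under either.

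**What to change.** - Rename the at-least-once measure as first use. State one conjunction and one denominator, identically in the Dose received text and in Table 3. If both components are required, say whether they must come from the same round.
- Define dose received as rounds completed divided by rounds delivered while the patient is in CopA. Show it by round (3, 6, 9 and 12 months), separately for PROMs and for home measurements.
- Align the fidelity row of Table 3 with the Fidelity text, so that 3-monthly PROM completion appears in both.

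The cost is definition wording, some additional descriptive tabulation, and a reported percentage that will probably be lower than the at-least-once figure. No new patient questionnaires or visits are needed. The fix assumes that the EHR weblog records each round and each component. The protocol says only that the weblog is generated automatically from the EHR, so this should be confirmed before the definition is fixed.

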##### Fidelity

Fidelity refers to the quality of the deliverance of an intervention and the extent to which the intervention was delivered as planned. We define fidelity in this study as the proportion of patients that filled out PROMs every 3 months for at least a year and received their 6-month appointment with the gynaecological oncologist. Furthermore, we will evaluate how often the answers of patients to the PROMs exceeded a threshold and what consequential actions were taken by the HCPs and/or patients. We will also determine the frequency and type of contact between the oncological nurse and the patient and the frequency of any additional appointments with a gynaecologist.

##### Participants’ attitudes

These will be assessed using the MIDI questionnaire and GEMS questionnaire (see under 1) and through interviews and focus groups (see under 2).

